### Study phases

Patients will be followed up for 8 weeks in phase I (acute treatment), 8 weeks in phase II (potentiation treatment) and shall continue in phase III (maintenance) until study endpoint at 2 years. Scale raters will be blind to the treatment. Only patients that respond will continue to phase 3, with response determined according to the initial symptoms score in phase I. Patients in phase III using quetiapine alone that present a new episode of any polarity, as detected on two consecutive visits, will start phase II (potentiation treatment). Patients that show no response after phase II will be dropped from the study.

The definition of clinical course is defined as follows: no response, reduction ≤25% in severity of symptoms; partial response, improvement of 26 to 49% in symptoms; response, reduction ≥50% in severity of symptoms; remission, minimal or no symptoms for at least 1 week, Hamilton Depression Scale ≤7 and Young Mania Rating Scale ≤9; sustained remission, ≥8 weeks of remission; relapse/recurrence, return of the signs and symptoms for the syndrome as per criteria; and worsening, return of symptoms at subsyndromal level [28-30].

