## Background

Bipolar disorder (BD) treatment is a focus of ongoing research to further understanding of the clinical features and possible pathophysiology of the disease. The multivariate factors associated with the etiology of BD, coupled with the variability of clinical presentation, hamper the determination of a specific treatment with optimized outcomes (efficacy and tolerability). Difficulties in BD treatment include delay in diagnosis, high levels of comorbidity, frequent treatment nonadherence and high risk of relapse/recurrence (particularly in the presence of residual symptoms) [1].

Most currently available treatments focus on the acute phase and use a reduction in symptoms ≥50% from baseline as a measure of response. In fact, some responders to treatment continue to experience significant subsyndromic symptoms. A small number of studies have reported remission rates, defined as ≥2 months with no significant signs or symptoms of the disorder [2]. Fewer studies, however, have reported remission during the acute phase through to the maintenance phase of treatment and its predictors [3], which are of great clinical significance. Recent data show that BD treatment under special conditions was associated with full remission in only one-half of the patients and that nearly one-half of the recovered patients relapsed at least once during a 2-year follow up [4]. Maintenance treatment is necessary in BD due to the high mortality, morbidity risk and social and professional impairment associated with poor outcomes [5].

As monotherapy, quetiapine has proven more effective than lithium in the treatment of depression at doses ranging from 150 to 600 mg [6,7], with no significant difference found between 300 and 600 mg doses [8]. The drug has also shown similar efficacy in the treatment of mania at doses of between 600 and 800 mg compared with lithium after 4 weeks and with haloperidol after 84 days [9-11], although response in mania was slower when compared with haloperidol [11]. To date, quetiapine is the only antipsychotic medication with evidence of efficacy across all phases of bipolar disorder [7], and was recently indicated as the first choice in monotherapy for the treatment of bipolar depression [12,13].

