### Interventions

After diagnostic assessments, the patients initiate treatment with quetiapine for 8 weeks as described above. For acute treatment, patients shall receive a starting dosage of 100 mg on day 1, to be increased by 100 mg/day to 300 mg on day 3. The 300 mg dose shall be subsequently adjusted until reaching the most effective dose according to clinical criteria. The patient dose shall be determined according to individual tolerability, and a maximum dose of 800 mg will be allowed for this study. Patients showing remission or >50% reduction in baseline scores on the Hamilton Depression Scale and the Young Mania Rating Scale shall proceed to the maintenance phase for a further 18 months. Patients showing score reductions <50% on the scales will be allocated to one of the arms of the augmentation phase. Group I will receive lithium at the standard dose: starting at 300 mg daily, the weekly dose will be adjusted according to blood serum level (between 0.5 and 0.8 mEq/l) according to efficacy and tolerability. Group II will receive aripiprazole: starting at 10 mg daily, the dose will be adjusted up to 15 mg daily according to efficacy and tolerability. The only concomitant medications permitted are lorazepam at doses of 0.5 to 4 mg/day and biperiden at 2 to 8 mg/day.

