### Primary outcomes

Primary outcome will consist of the evaluation of changes in mean scores on the CGI-BP-M between baseline and endpoint at the end of each phase of the study.

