### Planned analyses

The primary analysis will entail evaluation of mean scores on the CGI-BP-M between baseline and endpoint in both groups. In addition, differences shall be evaluated by comparing the two treatment groups according to the total number of patients in full remission at the study endpoint and the reason for and timing of drop out. Continuous data will be represented as mean and standard deviation whereas categorical variables will be described by a table of frequencies. The results of all statistical comparisons of the treatment groups will be expressed as two-sided *P* values rounded to three decimal places. The criterion for statistical significance in all comparisons will be *P* ≤0.05.

Continuous variables will be compared using repeated-measures of analysis of variance, with the treatment group and study phase as factors. Rates of response, remission and dropouts will be compared between the two groups using Pearson's chi-square test for categorical data. Dichotomous measures will also be compared using odds ratios and 95% confidence limits.

The correlation of clinical issues, quality of life, social adjustment and cognitive impairment will be evaluated by Pearson's correlation.

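### The planned repeated-measures ANOVA in its standard form omits randomised patients with no end-of-phase-III rating, and the article does not say whether those who relapse on an add-on are still rated

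*Protocol article*

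**What the plan says.** Under Primary outcomes, the article takes "changes in mean scores on the CGI-BP-M between baseline and endpoint at the end of each phase of the study". Planned analyses names the method: "Continuous variables will be compared using repeated-measures of analysis of variance, with the treatment group and study phase as factors". The same section also compares the number in full remission at the study endpoint, the reasons for and timing of drop-out, and the rates of response, remission and drop-out.

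Study phases fixes who reaches phase III and who is removed: "Only patients that respond will continue to phase 3, with response determined according to the initial symptoms score in phase I", and "Patients that show no response after phase II will be dropped from the study". Otherwise patients go on in maintenance to the two-year endpoint. On a phase III episode there is one rule, which covers "Patients in phase III using quetiapine alone that present a new episode of any polarity": once the episode has been seen at two visits in a row, they enter phase II. Relapse/recurrence is defined in that section, but the definition is tied to no follow-up or scoring consequence.

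The section on the design of the study makes prevention of relapse and recurrence the focus of treatment.

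**The concern.** Patients on quetiapine alone in phase III have not been allocated to lithium or aripiprazole. The only stated consequence of a phase III episode therefore applies to people outside the randomised comparison. For randomised patients who responded in phase II and then relapse, the article does not say whether blinded rating continues.

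That gap matters because of the analysis method. A standard repeated-measures ANOVA with phase as a within-patient factor needs a value for every phase, and a patient without the phase III value drops out of it. Some loss is foreseeable: phase II non-responders are removed by rule, Sample size and randomization acknowledges compliance difficulties in long trials, and Planned analyses expects drop-out. If relapse is one of the routes out, the last comparison leaves out the events that the treatment is meant to prevent. Ratings that were never taken cannot be recovered by a later analysis plan.

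**Working it through.** **1. The plan's own figure.** Sample size and randomization gives 25 per group, 0.8 SD, 5% significance and 80% power; Planned analyses gives two-sided P values. The normal approximation gives power 0.807 and the noncentral t gives 0.791. The stated 80% is reproduced, but it supposes that all 50 patients are analysed.

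**2. Power if patients lack the phase III score.** The article gives no loss rate, so equal loss in both arms is assumed, from any cause, with the effect held at 0.8 SD (two-sided t-test):

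| Loss | Left per arm | Power |
|---|---|---|
| 10% | 22.5 | 0.75 |
| 20% | 20 | 0.69 |
| 30% | 17.5 | 0.63 |
| 40% | 15 | 0.56 |
| 50% | 12.5 | 0.48 |

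**3. How much loss could be relapse.** The only relapse figure is in Background, from another study: "nearly one-half of the recovered patients relapsed at least once during a 2-year follow up". Assume exactly one-half and a constant hazard, ln(2)/24 per month.
- Over 12 months (phase III in the Abstract): 1 − 2^(−12/24) = 29%.
- Over about 20 months (two years less 16 weeks, from Study phases): 1 − 2^(−20/24) = 44%.

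Assume also that 40% to 70% respond in phase II, so that 10 to 17.5 per arm enter phase III. If every relapser left unrated, the losses per arm would be:

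| Response | Relapse | Non-responders | Relapsers | Left | Non-responders' share of loss |
|---|---|---|---|---|---|
| 40% | 29% | 15 | 2.9 | 7.1 | 84% |
| 40% | 44% | 15 | 4.4 | 5.6 | 77% |
| 70% | 29% | 7.5 | 5.1 | 12.4 | 59% |
| 70% | 44% | 7.5 | 7.7 | 9.8 | 49% |

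Relapse would account for about 6 to 15 of 50 randomised patients (2 × 2.9 to 2 × 7.7). In three of the four cases most of the loss comes from the separate removal of phase II non-responders; in the fourth it is about half.

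**4. What omitting relapsers does to the difference.** Let p₁ and p₂ be the relapse proportions, g the amount by which a relapser scores worse (the same in both arms), and d the arm difference among those who stay well. With all phase III entrants scored, the arm difference is d + g(p₂ − p₁). With relapsers omitted it is d. The part lost is g(p₂ − p₁).
- 20% versus 40%, g = 1 to 2 SD: 0.2 to 0.4 SD lost.
- 20% versus 50%, g = 1 to 2 SD: 0.3 to 0.6 SD lost.
- In CGI points, assuming a mean of 1.5 if well and 4.0 if relapsed: 30% versus 50% gives 0.20 × 2.5 = 0.50; 25% versus 55% gives 0.30 × 2.5 = 0.75.

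Setting d = 0 makes the remaining difference zero by construction. These figures show the mechanism and do not estimate it for this trial.

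**The case against.** The strongest reply is that nothing in the article withdraws a patient who relapses on an add-on. Study phases has patients continue to the two-year endpoint. The quetiapine-alone sentence can be read as an exception for those who still have an augmentation step available. On that reading the relapser stays, the blinded assessor rates the relapse, and the end-of-phase score records it. This stands, and it makes the harm conditional.

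Nor does the medication restriction ("The only concomitant medications permitted are lorazepam", with biperiden) force relapsers out, since the same section allows study-drug doses to be adjusted for efficacy and tolerability. Differential loss would also be partly visible in the planned drop-out and remission comparisons, although those do not put relapse into the CGI-BP-M result.

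A further reply is that scoring and missing-data rules belong in a full protocol or analysis plan that is not shown. That disposes of a complaint about the missing path taken alone. It does not dispose of the stated method: the article names repeated-measures ANOVA with phase as a factor, and a less bias-prone alternative is readily available. The article does not say how the ANOVA will treat incomplete patients, so its omission of them rests on the standard form.

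**Conclusion.** The point holds in a limited, conditional form. The named ANOVA, as usually run, omits randomised patients without a phase III rating, and the article does not say that add-on relapsers will be rated. If they leave unrated, the phase III comparison covers those who stayed well and may be attenuated by g(p₂ − p₁): 0.2 to 0.6 SD under the assumed relapse rates, against a design effect of 0.8 SD. The true size cannot be derived from the article, which gives no relapse or response rate for these patients.

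A reader might infer three stronger things that the article does not support:
- That the trial will lose its relapsers. No text removes them, and the default is continuation.
- That two add-ons with different relapse rates would look identical on the primary outcome, or that its sign is open. The zero comes only from assuming equal scores among the well, no reversal has been shown, and the outcome is also measured at the ends of the earlier phases.
- That relapse is what would shrink the arms to about 6 to 12 patients. On the assumed figures, 49% to 84% of that loss is phase II non-response, a separate matter.

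This is an inexpensive improvement of minor severity.

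**What to change.** 1. **Planned analyses:** replace the repeated-measures ANOVA for CGI-BP-M with a mixed model using all post-randomisation ratings from all randomised patients, so that no one is omitted for lacking the last phase.
2. **Study phases:** state that randomised patients with a phase III episode are rated by the blinded assessor at the visit confirming the episode and, if they agree, at the scheduled end of phase III, whatever treatment follows.
3. **Response and remission:** keep all randomised patients in the denominator at the study endpoint.

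The cost is some wording, a different model, and a rating for patients who would otherwise leave. There are three drawbacks. Scores after a relapse reflect the add-on strategy rather than the drug alone. Endpoint response and remission proportions may look lower. The mixed model assumes that data are missing at random, and for phase II non-responders who are removed it relies on their earlier ratings. No treatment rule is proposed.

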### Primary outcomes

Primary outcome will consist of the evaluation of changes in mean scores on the CGI-BP-M between baseline and endpoint at the end of each phase of the study.

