**Methods/Design:**

The ARIQUELI study is a single-site, parallel-group, randomized, outcome assessor-blinded trial. BD I patients according to the DSM-IV-TR, in depressive, manic/hypomanic or mixed episode, aged 18 to 40 years, are eligible. After diagnostic assessments, patients initiated treatment in phase I with quetiapine. Nonresponders or partial responders after 8 weeks are allocated into one of two groups, potentiated with either lithium (0.5 to 0.8 mEq/l) or aripiprazole (10 or 15 mg). Patients will be followed up for 8 weeks in phase I (acute treatment), 6 months in phase II (continuation treatment) and 12 months in phase III (maintenance treatment). Outcome assessors are blinded to the treatment. The primary outcome is the evaluation of changes in mean scores on the CGI-BP-M between baseline and the endpoint at the end of each study phase.

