### Sample size and randomization

Sample size was calculated by comparing the mean difference in Clinical Global Impression for Bipolar Disorders (CGI-BP-M) scores between baseline and endpoint for the two groups. Comparison using Student's *t* test showed that a sample of 50 patients (25 in each group) attains an 80% power (at 5% significance level) for detecting a difference of 0.8 standard deviations, considered a large effect size [27]. Owing to the exploratory nature of this study and the difficulties regarding compliance in long-term trials, this was deemed an acceptable value [27].

The random allocation sequence was computer generated by a biostatistician. Patients were enrolled by clinicians who have their code revealed by the research monitor when assigned to interventions. Blinding of outcome assessors is ensured by keeping their evaluations independent from those of the clinicians.

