### Secondary outcomes

Secondary outcome will include the proportion of patients that achieve remission and response to each treatment at the end of each phase of the study, according to improvement on the rating scales (Hamilton Depression Scale; Montgomery–Åsberg Depression Rating Scale; Young Mania Rating Scale) and in CGI-BP-M [31]. The CGI-BP-M is a clinician rating scale modified for BD for assessing treatment response and consists of three subscales evaluating severity of mania, depression and global disease symptoms.

Other outcome parameters include safety and tolerability, quality of life and social adjustment, and cognitive impairment. These parameters will be evaluated by comparing the endpoint measures for each phase with baseline values. Safety and tolerability were determined according to the clinical evaluation of adverse effects and score on the UKU side-effect rating scale [32]. The UKU comprises a 48-item clinician rated scale evaluating side effects in psychic, neurologic, autonomic and other domains. Quality of life and social adjustment were measured with the WHOQoL-BREF [33] and the Social Adjustment Scale [34]. These instruments were previously translated and validated into Portuguese [35,36]. The WHO-QOL-BREF is a 26-item self-report scale comprising four domains: physical, psychological, social, and environmental. The Social Adjustment Scale is a 54-question self-report instrument that measures instrumental and expressive role performance over the previous 2 weeks. Cognitive impairment was measured neuropsychological tests (Wisconsin Card Sorting Test, Stroop Color Word Test [37], Wechsler Abbreviated Scale of Intelligence [38], Trail Making Test [37] and others), for which versions are available in Portuguese. All investigators received appropriate training, and inter-rater reliability is periodically assessed.

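### No single phase, CGI-BP-M score or model effect is named as the primary test, so the 5% level and the power behind 25 per group hold only if one is chosen

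*Protocol article*

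**What the plan says.** - **Outcome.** The section Primary outcomes sets the endpoint as "changes in mean scores on the CGI-BP-M between baseline and endpoint at the end of each phase of the study". The Abstract says the same in substance. No phase is given priority.
- **Instrument.** The section Secondary outcomes explains that the CGI-BP-M "consists of three subscales evaluating severity of mania, depression and global disease symptoms". Nowhere is one of these scores chosen as primary, and no total is defined.
- **Threshold.** Planned analyses states: "The criterion for statistical significance in all comparisons will be *P* ≤0.05". No order of testing or adjustment accompanies this rule.
- **Model.** Planned analyses describes the primary analysis as baseline versus endpoint in both groups. It compares continuous variables by repeated-measures ANOVA with arm and phase as factors. It does not say whether the arm effect or the arm-by-phase interaction is decisive, or which phases are levels of the factor.
- **Sample size.** Sample size and randomization says that 25 per group "attains an 80% power (at 5% significance level) for detecting a difference of 0.8 standard deviations", using Student's t test.
- **Allocation.** In the Abstract, "Nonresponders or partial responders after 8 weeks are allocated into one of two groups". In Interventions, "Patients showing score reductions <50% on the scales will be allocated to one of the arms of the augmentation phase". Both place allocation after the 8 weeks of quetiapine alone.
- **Phases.** Study phases says "Patients will be followed up for 8 weeks in phase I (acute treatment), 8 weeks in phase II (potentiation treatment"), with phase III following to 2 years. Only responders go on to phase III, and those without a response after phase II leave the study. The Abstract gives phase II as 6 months.

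**The concern.** The sample size describes a trial with one primary comparison at 5%. The outcome definition and the blanket threshold allow several. If the primary result may be read at more than one phase, on more than one subscale, or from more than one model effect, each at 0.05, the chance of at least one false-positive primary finding exceeds 5%, and the power calculation no longer matches the claim.

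The choice has practical weight here. Patients enter in depressive, manic/hypomanic or mixed episodes, so the mania and depression scores can move differently, and the more favourable one could be put forward afterwards.

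Two of the three phases are also awkward as primary time points. At the end of phase I nobody has yet been allocated to lithium or aripiprazole. In phase III the patients under comparison have been selected by their response after randomisation.

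**Working it through.** **1. Reproduce the plan's own figure.** Inputs from Sample size and randomization: difference 0.8 SD, 80% power, 5% level; two-sided, from Planned analyses.

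Normal approximation: n per group = 2 × (1.960 + 0.842)² / 0.8² = 2 × 7.85 / 0.64 = 24.5, so 25. Power at 25 per group is 80.7%. With the exact noncentral t (48 degrees of freedom, noncentrality 0.8 × √(25/2) = 2.83), power is 79.1%, and 26 per group are needed for 80%. The stated 50 is reproduced, for one test.

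**2. Count the tests that the text leaves open.** Arms exist only in phases II and III, so two phases can carry a randomised comparison. There are three subscales. The readings are:
- one score at both phases: 2 tests;
- three subscales with one test each (for example one ANOVA effect per subscale): 3 tests;
- three subscales at both phases: 6 tests.

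**3. Chance of at least one false positive.** If independent, it is 1 − 0.95^k. For correlated tests, 400,000 draws of equicorrelated normal statistics were simulated, each tested two-sided at 0.05. The documents give no correlation, so the values below are assumptions.

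| Tests | Independent | 0.3 | 0.5 | 0.7 | 0.9 |
|---|---|---|---|---|---|
| 1 | 5% | – | – | – | – |
| 2 | 1 − 0.9025 = 9.75% | 9.5% | 9.1% | 8.4% | 7.1% |
| 3 | 1 − 0.8574 = 14.3% | 13.5% | 12.5% | 10.9% | 8.3% |
| 6 | 1 − 0.7351 = 26.5% | 24.1% | 20.7% | 16.4% | 10.8% |

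Every reading with more than one test exceeds 5%.

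**4. What keeping several primary tests would cost.** With Bonferroni and a true difference of 0.8 SD (exact t):

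| Tests | Level per test | Power per test at 25 per group | n per group for 80% |
|---|---|---|---|
| 2 | 0.025 | 69.6% | 31 |
| 3 | 0.0167 | 63.7% | 35 |
| 6 | 0.0083 | 53.5% | 40 |

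**5. Phase I as a level of the phase factor.** Suppose the true difference is 0.8 SD at the end of both phase II and phase III, and zero at the end of phase I because treatment has not yet diverged. An arm effect averaged equally over three levels is (0 + 0.8 + 0.8) / 3 = 0.53 SD, on the single-phase scale. Including phase I thus takes one third off the effect being estimated.

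**The case against.** Several stronger readings are tempting, and the article does not support them.

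- **Three declared co-primary subscales.** No section says this. The sentence on subscales describes the instrument and stands under Secondary outcomes. The fair statement is that no score is chosen.
- **A separate test at every phase.** The stated analysis is a repeated-measures ANOVA containing phase as a factor, which may combine the phases in one model. Counts of two or six tests are therefore possible readings, not written plans.
- **A between-arm primary test at the end of phase I.** None is planned. Change over phase I may be meant as a description of a single cohort. A count of nine tests (1 − 0.95⁹ = 37%) should not be used.
- **Any significant result counts as success.** The article gives a general significance criterion, not a success rule. The percentages measure what the wording permits.
- **Inflation to several times 5%.** Only the upper end of the six-test reading gives that, and it requires independence. A global score rated beside mania and depression scores in the same patients is unlikely to be independent of them.

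It can also be said that the study calls itself exploratory and that an analysis plan may settle the detail. The first remark is used to justify the effect size and sample; it does not relax the 5% level. On the second, scoring and modelling detail may indeed lie elsewhere, but this document itself fixes a primary outcome at each phase and one threshold for everything. Reading endpoint in Planned analyses as study end alone would give one time point, but it would conflict with Primary outcomes and still leave the score open.

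**Conclusion.** The concern holds in this form: the primary outcome spans all phases, all comparisons are judged at 0.05, and no phase, score or ANOVA effect is designated as the primary test, although the trial is sized for one. The 5% level and the roughly 80% power are valid only once a single test is chosen.

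Otherwise the chance of a false-positive primary result is about 7% to 26%, depending on how many tests are read into the text and on correlations that the documents do not give. No single figure within that range can be claimed. The sample-size arithmetic is sound for what it describes.

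Two features do not depend on any correlation. The end of phase I carries no randomised comparison and would dilute a pooled arm effect. The phase III comparison is not of all randomised patients.

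**What to change.** Name one primary test: one score, one post-randomisation time point, one contrast. One example is CGI-BP-M global severity at the end of the augmentation phase, lithium versus aripiprazole, in all randomised patients, two-sided 0.05. The stated 25 per group then stands (79.1% power by exact t, 80.7% by normal approximation).

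Make the mania and depression subscales and the phase III results secondary, either Holm-adjusted or labelled descriptive. Report phase I descriptively, and do not let it enter the between-arm effect.

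Reconcile the length of phase II, which is 6 months in the Abstract and 8 weeks in Study phases; until then the end of that phase is not a fixed time point.

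Another single choice could be defended. The design section stresses relapse prevention and long-term follow-up, for example. A phase III primary would, however, have to deal with the selection of responders.

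**Cost.** No more patients are needed. But the article reports patients already in all three phases, so this is a substantive mid-trial decision. It should be documented and dated before any comparison by arm. Phase III and the other subscales can then no longer be claimed as primary.
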